## Abstract

**Background:**

Behavioral intervention is a key approach to HIV prevention among men who have sex with men (MSM). Widespread use of mobile phones provide us with novel opportunities to decrease HIV infection and transmission of MSM. The objective of the study was to design and develop a mobile phone application (app) aims to conduct behavioral intervention to MSM and to evaluate the efficacy of the app-based intervention compared to usual care, to analyze cost-effectiveness and mechanism of the intervention.

**Methods:**

This study involves 2 phases, phase 1 use qualitative method and phase 2 is a randomized controlled trial lasting for 18 months, they will be conducted in Chagnsha, Hunan Province, China. Phase 1 is to design and develop the app, procedures including retrieval of domestic apps related to prevention and treatment about HIV and sexually transmitted diseases (HIV/STDs), personal interviews with MSM about preferences and functional needs of the HIV prevention app, multidisciplinary experts focused group discussions of the app, software engineers’ development and users test of the app will be performed. In phase 2, we will recruit 800 MSM by cooperating with the local center of disease control and prevention and nongovernmental organizations, and divide them into intervention and control group evenly. Intervention group participants will receive app-based HIV prevention. Control group participants will be provided with usual care including HIV/STDs knowledge brochure and free voluntary counseling services. Data will be collected at baseline, 6, 12 and 18 months since subject’s participation. Effectiveness of the intervention includes HIV/STDs infection rates, adherence to regularly HIV testing, sexual risk behavior, consistent condom use and relative risk of HIV infection. Cost-effectiveness will be analyzed by decision-analytic modeling, and mechanism analysis of this app-based intervention will be performed by path analysis.

**Discussion:**

This will be the first study of its kind in China to develop an app and implement app-based HIV prevention intervention among MSM. It is of great potential to determine whether app-based intervention is a cost-effective way to decrease HIV infection among MSM and explore intervention mechanism with an accurate method.

**Trial registration:**

Chinese Clinical Trial Register (ChiCTR-IOR-15006724). Registered 10 July 2015.

## Background

Men who have sex with men (MSM) have been identified as high risk population of HIV infection and transmission since the world’s first AIDS case found in the United States at 1981 [1], and studies about HIV prevention among MSM had not been paid enough attention by Chinese researchers until the first case of AIDS patient in China found at 1985 [2]. HIV prevalence among MSM population has been continuously increasing at a rapid speed [3, 4]. In China, the proportion of HIV infection among MSM population jumped from 1.4% in 2001 to 6.3% in 2011 [5]. In 2007, MSM accounted for 12.2% among all of the yearly found new HIV infection cases, but this percentage soared to 29.4% in 2011 [6]. And in Changsha, Hunan Province of China, 46% of the yearly found new HIV cases are MSM (Changsha CDC). MSM have become the key population of HIV prevention interventions.

Despite scientists’ ongoing efforts to explore biomedical techniques of HIV prevention such as vaccine development, circumcision, antiviral drug use and so forth [7–9], behavioral interventions are still regarded as key approaches to HIV prevention [10, 11]. These involve regularly HIV testing, free condom providing, health education (e.g. peer education), individual behavioral and mental health counseling [12–17], etc. They have been proved to be effective of improving MSM’s health behaviors, finding newly infected individuals timely and referring them to rapid care and treatment services. Lots of existed studies involved an intervention package which consists of more than one way of behavioral intervention [18, 19]. However, since most of the interventions were performed by face-to-face patterns, there were three limitations which may constrain their effects. (1) High financial cost, labor consumption, and time consuming, (2) narrow coverage of MSM group, and (3) unsatisfying intervention adherence [20]. So it is imperative to explore more effective, extensively accessible, economic and comprehensive HIV prevention tools and strategies [21].

The contemporary world has been greatly changed by the Internet. And the Internet supported interventions have been regarded as “*disruptive innovations*” and become new weapons by researchers and health providers when it comes to HIV prevention [22]. The internet-based interventions have 3 irreplaceable advantages over face-to-face delivered interventions, (1) these interventions can be broadly diffused and maintained at lower financial and personnel cost, (2) the Internet’s characteristics like anonymity and information confidentiality can improve acceptability of the interventions among MSM, (3) the interactive functionality of the Internet gains popularity among different populations, especially among those hard-to-reach groups [23, 24].

Online surveys can provided us with a large amount of information about MSM’s sexual behaviors and mental health in a short period of time, giving auto reminders of HIV testing to clients, conducting motivational interviews about behavior changing and health skills promoting, and performing health education by using websites [25–28]. Levine and colleagues developed an online partner notification system *inSPOT* to inform sex partners of the HIV-positive person to take HIV test [29]. In China, gay websites often be used as tools for health behavior collecting, education delivering, and as a recruiting method for intervention outreach to offline sites [30–32]. Guangzhou CDC of China cooperated with a gay website named Guangtong website to develop a web platform named *Easy Tell* to do anonymous partner notification [33]. Effects of these Internet-based HIV prevention interventions were proved to be comparable to those face-to-face interventions, and they were more accessible and acceptable.

Mobile network is the combination of mobile communication devices and the Internet, mobile phone application(app) is the typical type and current trend of mobile network [34]. Six-hundred fifty-six million Chinese are currently using mobile phones to link to the Internet [35], and it is estimated that 6.72 to 16.8 million of them are MSM. Comparing with computer network, mobile network has more strength, especially with the users online almost 24/7, we can make the intervention to penetrate into the users daily lives. And because of the personal privacy of mobile phone, the intervention can be more targeted and individualized. Besides, personal behavioral data can be collected easily by mobile network due to its portability and access to sensing devices, the big data collected can be analyzed to explore the mechanism of the intervention, which previous studies cannot hold a candle to.

It was consumed that app-based interventions have great potential to become a vital window for health maintenance and promotion of MSM [36]. Several qualitative studies conducted by MSM focus group discussions demonstrated preferences and functionality of HIV prevention app. The app should include educational content like information about HIV testing and prophylaxis distribution institutions and groups, HIV/STDs diagnose and treatment information, drug and alcohol abuse risk and safer sex skills. Interactive engagement such as connection with gay-friendly health providers, other HIV-positive gay men, and support peers/groups. Usability of the app is the most important feature because the app would not be of value if MSM do not use it, which means MSM feel useful, safe and trustworthy about the app’s language and confidentiality [24, 37, 38]. Our previous studies found that mobile phones were widely used among MSM, it was popular for MSM using the gay tailored dating apps such as Grindr, Jack’D, and domestic apps like Blued, ZANK for speed dating, casual sex, or even group sex. Lots of Chinese MSM expressed urgent need of humanistic care, professional mental and behavioral health services, and welcome interventions using the app, Wechat and other mobile network media with open arms [39, 40]. However, there is no MSM tailored, app-based HIV prevention emerged so far.

The objectives of the study are to (1) design and develop an easy to use, user-friendly, non-stigmatized and free app, and deliver app-based HIV prevention intervention to MSM, and (2) to evaluate the effectiveness of the app at decreasing rate of HIV infection, promoting HIV testing behavior and consistent condom use among MSM, and cost-effectiveness analysis of the intervention. App-based intervention mechanism will also be explored.

## Methods

### Study design

This study comprises 2 phases. In phase 1, qualitative method is employed for designing and developing the app. Functional modules of the app are designed on the basis of (1) a retrieval of currently exist HIV/STDs prevention and treatment related apps, (2) personal interviews with MSM about preferences and function needs of the app, and (3) periodical meetings of a multidisciplinary team. Fifty MSM will be invited to test the app after completion of app development and modifications will be made according to their use experience and advice. Phase 2 is a randomized controlled trial lasting for 18 months, to evaluate effectiveness of the app-based intervention and to explore intervention mechanism. Eight-hundred MSM will be recruited and evenly divided into the intervention arm and control. Participants in the intervention arm will receive app-based HIV prevention intervention, and the control arm individuals will receive usual care service which includes free health education materials, voluntary counseling and testing services.

### Setting

Subjects recruitment will be performed in Changsha, provincial capital of Hunan province, China. The city has over 6 million people, including 15 thousand MSM. Implementation of this study will be cooperated with Chagnsha CDC. It is the authoritative HIV testing institution, and has the right to verify one’s HIV-positive status. In addition, the center takes charge of two non-governmental organizations (NGO) which exclusively providing HIV testing and counseling services for MSM. These organizations have built good relationship with MSM.

## Participants

### Inclusion and exclusion criteria

Participant inclusion criteria: (1) male aged 16 years or older, (2) has experience of same-sex anal intercourse during the last 12 months, (3) HIV negative, (4) own at least one smartphone, and (5) willing to report individual HIV/STDs testing results to the researcher. Participant exclusion criteria:(1) has only one sex partner who is also HIV negative, and their relationship has last for more than 2 years, (2) unable to participant the program because of cognitive or psychiatric disorders, or (3) has already attended another intervention program.

### Recruitment

For the participant enrollment, in phase 1 and phase 2, MSM who are potential eligible for the study will be listed, and each individual will be invited to take free HIV testing and participate in the study through phone call performed by the staff of CDC and the two NGOs. An appointment will be made if the person agrees to participate. Following an oral informed consent, clients will be screened for eligibility as subjects of the study by a research member, demographic information and baseline data(details below) will be obtained, and blood samples will be taken for HIV testing. Written informed consent will be obtained from each one who is HIV-seronegtive and willing to participate in the study. Those HIV-seropositive persons will be referred to local CDC for verification and treatment.

### Randomization and blinding

Participants in the randomized controlled trial will be assigned 1:1 to the intervention and control arms under restricted randomized block design (the block length is 4) after informed consent and collection of baseline data. The allocation sequence will be generated and released to the interventionist on a case-by-case basis by another independent department specializes in generating research random sequence. The recruitment staff have no access to the results of randomization prior to recruiting the subject. Participants will be informed of his group by a research assistant by phone. Interventionist, data collection staff, statistician are not the same persons. This is a single-blinded trial. The subjects cannot be blinded due to the nature of the intervention, and interventionist also acknowledge all those contacted are in the intervention arm. But anonymous responses will be entered into the database by a person unconnected with the project. The statistician will be blinded to individual result during the intervention period, and the allocation-to-trial-arm coding will not be revealed until dataset is sealed. The interventionist and supervisors will be blinded to the baseline and follow-up outcomes.

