## Discussion

In line with goals of implementation science, the study is going to develop a mobile phone app which comprises of behavioral, psychological and social services and for MSM, and implement a randomized controlled trial of HIV prevention intervention by using this app among MSM and evaluate effectiveness of the app-based intervention. The goals of the intervention are to provide MSM with health information, encourage their motivation of behavior change and promote their health skills.

It has been shown that apps are beneficial to self-management of people with chronic conditions, physical activity promotion among different age groups, and other health related behaviors [44–46]. There were systematic reviews pointed out that apps have great potential as tools for HIV prevention among MSM, and there were also studies on MSM’s acceptability and preferences of app-based. However, there is no randomized controlled trial targeting at MSM group with an app. This is the first study of its kind.

There are several strengths of the study. Mobile network is the combination of the Internet and mobile devices, and has the advantage of higher portability. The “always online” feature made it become a part of one’s daily life. Mobile phone can protect personal privacy and realizes point-to-point individualized intervention as well, which provide us with a better and accurate way to illustrate intervention mechanism. The long-term follow-up makes it possible to observe intervention effects with more persuasive results. And the cost-effectiveness analysis will help policy makers perform informed and practical decision-making.

As for the limitations of the study design, due to the open design we cannot mask the intervention, participants will be aware that they are in a HIV prevention intervention, which may introduce bias. Randomization allocation of participants into different groups can help achieve balance in sociodemographic characteristics. And researcher in charge of statistical analysis will be blinded to group allocation.

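### A single published block length of 4 in an open trial leaves up to one third of allocations deducible by anyone who knows the earlier ones; varying the block size at random is a nearly free safeguard.

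*Protocol article*

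**What the plan says.** All references are to the protocol article.

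- **Randomization and blinding:** "Participants in the randomized controlled trial will be assigned 1:1 to the intervention and control arms", under a "restricted randomized block design (the block length is 4", after consent and baseline data. No variation of the block length is mentioned, and no stratification.
- **Same section, safeguards:** a separate department generates the sequence and releases it to the interventionist one case at a time. Recruiters have no sight of a man's result before he is recruited. The interventionist, data collection staff and statistician are different people.
- **Same section, openness:** "The subjects cannot be blinded due to the nature of the intervention"; the "interventionist also acknowledge all those contacted are in the intervention arm"; and "Participants will be informed of his group by a research assistant by phone". The Discussion concedes that "due to the open design we cannot mask the intervention".
- **Recruitment:** potentially eligible men are listed and each is invited "through phone call performed by the staff of CDC and the two NGOs". Screening by a research member, baseline data, an HIV test and written consent follow.
- **Study design:** "Eight-hundred MSM will be recruited and evenly divided into the intervention arm and control".

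**The concern.** Concealment has two parts. The next assignment must be hidden from direct view, and it must not be inferable from earlier ones. The article deals with the first part. For the second it fixes one short block length, prints it, and says nothing about keeping past assignments or that length from the people who recruit or screen.

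Past assignments are not secret within the study. Each man is told his arm, a research assistant makes that call, and the interventionist knows who is in the intervention arm. The sentence separating roles names the interventionist, data collection staff and statistician. It does not name recruiters or the research member who screens. Blinding the statistician has no bearing on who is enrolled.

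If someone with influence over enrolment could work out the next arm, the type of man entering each arm could drift. The Discussion relies on randomization for balance in a trial it accepts is unmasked, and predictable allocation would weaken that protection.

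**Working it through.** The article gives no figure for predictability, so there is none to reproduce.

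**Inputs**
- Block length 4 and 1:1 allocation, so 2 men per arm in each block (Randomization and blinding).
- 800 men (Study design), so 800 / 4 = 200 blocks.
- Assumption: one unstratified sequence, since no strata are mentioned.

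**Full knowledge.** The observer knows all earlier assignments in order and where each block starts. A 2:2 block has 6 equally likely orders.
- In 4 orders only the last place is certain. In the other 2 (AABB and BBAA) the third and fourth places are both certain.
- Expected certain places per block: (4 × 1 + 2 × 2) / 6 = 1.333.
- Share: 1.333 / 4 = 33.3%. Of 800: 200 × 1.333 = 267.
- By place, the probability of certainty is 0, 0, 1/3 and 1. The last place alone gives 200 of 800.

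**Best guess under full knowledge** (name the arm less used so far in the block). The chances of being right, by place, are 1/2, 2/3, 2/3 and 1. Sum 2.833; 2.833 / 4 = 70.8%, against 50% with no information.

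**Partial knowledge.** Suppose each earlier assignment is known independently with probability p, and block starts are still known.
- Place 3 is certain if the first two went to the same arm (1/3) and both are known: p²/3.
- Place 4 is certain if both men in the arm already filled are known: p².
- Share: (p²/3 + p²) / 4 = p²/3.

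| p (assumed) | Certain share | Of 800 |
|---|---|---|
| 1 | 33.3% | 267 |
| 1/2 | 8.3% | 67 |
| 1/3 | 3.7% | 30 |

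The value p = 1/3 would fit a recruiter who knows only his own organisation's men, if the CDC and the two NGOs recruited equally. The article states neither.

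**Effect of varying the block size.** These are simulations of 800 allocations. The observer knows all past assignments and the set of possible sizes, but not the size of each block.

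| Block sizes | Certain | Best guess correct |
|---|---|---|
| 4 fixed | 33% | 71% |
| 4 and 6 at random | 5% to 6% | 69% |
| 4, 6 and 8 at random | about 2% | 68% |

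A longer fixed length known to staff helps less: 25% certain with length 6 and 20% with length 8, by the same enumeration.

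**The case against.** The strongest reply is that the article does not give recruiters what they would need.

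- **Knowledge.** Assignments go from the independent department to the interventionist, and a research assistant tells the participant. Nothing gives CDC or NGO callers any man's arm, let alone every arm in order across three organisations. That a man knows his own arm does not mean the caller does. This stands, and it makes one third a ceiling and not an estimate.
- **Control.** A reader might infer that callers choose whom to phone next and so steer men into the app arm. The Recruitment section does not support that: men are listed and each one is invited, with no stated discretion over order. Appointment, consent, screening by someone described as a research member, baseline data and an HIV test lie between the call and allocation, and men drop out at each step. Call order is therefore not allocation order. The screener is closer to allocation, and the article does not say whether that person knows earlier assignments.
- **Consequence.** A reader might also infer a bias that no analysis could remove. That goes too far. Baseline data precede assignment, so measured imbalance could be seen and adjusted for. Only selection on unmeasured features would remain.
- **Remedy.** Varying the blocks lowers best-guess success by only 2 to 3 percentage points. This also stands. The gain lies in the certain allocations.

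The reply does not answer why the block length should be fixed and published. The stated safeguards hide the coming assignment from view but do not prevent its deduction from earlier ones.

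**Conclusion.** The point holds as a low-priority improvement to a stated design rule. With a fixed block of 4, at most one third of allocations (about 267 of 800) are deducible with certainty and 71% can be guessed. Both figures assume a single unstratified sequence, complete knowledge of earlier assignments in order, and known block starts. Under assumed partial knowledge of 1/3 to 1/2 the certain share is about 4% to 8%, or 30 to 67 men.

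The article does not establish that anyone who recruits or screens has such knowledge or could act on it. What it leaves open is an avoidable risk of selection at enrolment; it does not show that selection bias will occur.

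**What to change.** Before enrolment, have the independent department regenerate the list with block sizes that vary at random, for example 4, 6 and 8. Keep the sizes from recruitment, screening and intervention staff until enrolment ends. Replace the stated length with a sentence saying that sizes vary and are withheld. Add that those who recruit or screen are not told earlier assignments; this also limits the guessing that varied blocks leave largely intact.

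The cost is a new list. With blocks of 4, a total of 800 ends in exact balance. With blocks of up to 8, stopping partway through a block can leave the arms at most 4 men apart, which is negligible beside 400 per arm.

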## Procedures

### Phase 1: Development of the app

First, on the basis of our previous studies and references reviewing, preliminary functional modules of the app were presented in Table 1 below. Next step of this study is to search and evaluate currently exist domestic HIV/STDs prevention and treatment related apps on Apple.

**Table 1 Tab1:** Function modules of HIV prevention app for MSM

Name	Function description
Behavioral assessment	Assessment about user’s unprotected sex behaviors and condom use rate
Behavior change plans	Setting personal goals and plans of health behavior change, and individualized reward/punishment plans
Counseling	Buttons for enter into phone, message, Wechat and email counseling areas
Health education	Knowledge about HIV diagnosis, prevention and treatment, skills of condom using, etc
Personal health records	Uploading HIV/STDs testing results, building personal health records and health promotion plans
Information push	Delivering latest news HIV prevention, treatment and related policies, and reminders of personal behavior, encouragement and advice
Experts encouragements	Videos from professionals and celebrities to encourage user’s adherence to behavior change efforts
Institutions introduction	Providing information about addresses, connection methods, providers and services offered of CDC, hospitals, NGOs nearby
Feedback platform	Building a communication platform where users can give feedback of using the app
Setting	Settings of time period of receiving information, passports of log in the app, latest versions, etc

Store and Android Market since the two markets occupy 90.61% of the current mobile application markets [41]. We use the words “HIV/AIDS/human immunodeficiency virus/STD/ sexually transmitted disease/sexual health/sexual behavior/positive sex/condom” respectively to search for related apps, each eligible app will be downloaded and its features, including names, download numbers, target population, main function modules will be listed and analyzed.

Second, personal face-to-face interviews with MSM will be conducted by using a semi-structured outline, which involves questions about currently confronting behavioral, mental and social problems, promotion and barrier factors of taking HIV test, ever used or currently using MSM tailored apps and their characteristics, preferences of name, logo, and functional needs about a HIV prevention app especially for MSM. Sample size of the interview process will depend on the information saturation rule which means as sample expanding, no new theme be induced from information the participants supplied. A functional framework will be built based on the two processes.

Third, periodical focused multidisciplinary experts group sessions will be held to discuss the framework of the app from the interactivity, feasibility, acceptability and user experience aspects. Finally, functional modules of the app will be determined. The app will be developed by a company specialized in mobile application development. After the app development completed, 50 MSM will be invited to test it, necessary modifications will be made according to their advice.

